##### **4.6.2 Statistical analysis**

All statistical analyzes will have a significance level of 5%. Paired-samples t-tests (also called dependent T-tests) will be used for the outcome of mean INR and PT. Analysis will be performed by protocol for these outcomes i.e., data from patients who start treatment with any drugs that interact with warfarin as previously defined (list in Annex II) will be excluded from the final analysis.

The dichotomous outcomes (TTR, thromboembolic events, bleeding) will be analyzed by McNemar's test. Exploratory analyzes for patient subgroups are not planned. The dichotomous variables will be analyzed by intention to treat, considering the missing data as an unfavorable outcome, in which case a sensitivity analysis will be carried out to assess the robustness of the result.

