## 4. Methods

#### 4.1 Type of study

Randomized crossover controlled trial containing six treatment sequences and divided into four phases with different durations (Figure 1). The study is registered in [www.clinicaltrials.gov](http://www.clinicaltrials.gov) under the identification NCT02017197 and also has the Universal Trial Number (UTN) U1111-1155-4833.

[figure not shown]

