#### **4.4 Procedures**

Patients will be randomly allocated to one of the treatment sequences (A, B, C, D, E or F, Figure 1) and will start treatment with either the branded warfarin sodium or with one of the two generic versions available in the Brazilian market in August 2013. The first phase of the study will last 21 days. During this period, the patient, who had already been using warfarin, will start the randomly allocated treatment that will also be used in the second phase of the clinical trial. The use of the same treatment in phases one and two aims to avoid the carry-over effect without the interruption of anticoagulation treatment, which would be ethically unacceptable. The duration of three weeks for this phase is equivalent to about seven warfarin half-lives (38), the washout time for elimination of this drug. The duration of this phase will allow us to ensure that the formulation of warfarin used previously does not interfere with the results of the trial.

The second, third and fourth phases of the study will last 28 days each, in order to allow more weekly measurements to assess the effect of therapy with each of the formulations. In the second phase the patients will continue with the treatment started in phase one, and in the third and fourth phases will occur the change of warfarins according to the predetermined sequences for each group.

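### The paired t-tests for mean INR and PT carry no phase term, which costs some precision in this six-sequence crossover and allows a small bias if losses differ by starting product

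*Protocol*

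**What the plan says.** Section 4.1 describes a "Randomized crossover controlled trial containing six treatment sequences and divided into four phases with different durations". Section 4.4.2 names three products, one branded and two generic. Section 4.4 sets out the phases:

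- Phase 1: "The first phase of the study will last 21 days". It uses the product that is then continued in phase 2, and the stated reason is that "The use of the same treatment in phases one and two aims to avoid the carry-over effect".
- Phases 2 to 4: "The second, third and fourth phases of the study will last 28 days each", and "in the third and fourth phases will occur the change of warfarins according to the predetermined sequences for each group".

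For the primary outcome and for PT, section 4.6.2 states that "Paired-samples t-tests (also called dependent T-tests) will be used for the outcome of mean INR and PT". The protocol nowhere mentions a phase, period or sequence term.

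Patients can leave the analysis after allocation in two ways. Section 4.3.2 removes those whose TTR in phase 1 is below 70%, a phase spent on the first allocated product. Section 4.6.2 removes those who start an interacting drug. Section 4.6.1 requires 48 patients and recruits 60.

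**The concern.** In a crossover, each patient's product difference is also a difference between two phases. Anything that moves INR in one phase for all patients, whatever they take, therefore enters that difference. A paired t-test cannot separate the two.

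The phases are not alike here. Phase 2 alone follows a period on its own product and comes straight after a selection on INR control. Dose is adjusted throughout (section 4.4.2). A shift common to one phase is therefore possible, though the protocol gives no evidence that one exists or how large it would be.

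Two things are at stake. With balanced sequences, precision is lost on all three product comparisons. With unequal losses by starting product, part of the phase shift appears as a product difference or hides one.

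**Working it through.** **Inputs from the protocol.** SD 0.29, difference 0.49, two-sided 5%, power 90%, 48 evaluable patients (8 per sequence), 60 recruited (10 per sequence). Sources: sections 3 and 4.6.1.

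**Assumptions.** The six sequences are all orders of the three products. Phase 2 mean INR differs from phases 3 and 4 by d, the same for every patient. The within-patient correlation is ρ. The protocol gives neither d nor ρ, so ranges are shown.

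**The plan's own figure.** 2 × [0.29 × (1.960 + 1.282) / 0.49]² = 7.36, so 8 per group and 8 × 6 = 48. Also 48 / 0.80 = 60, which allows for 12 losses. The stated sample size reproduces and is not in dispute here.

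**Balanced sequences.** Call two products A and B. Over the six orders, the phase shift contributes +d, +d, −d, −d, 0, 0 to A − B. The mean is 0, so there is no bias. The mean square is 4d²/6 = 2d²/3.

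The SD of paired differences without a phase shift is 0.29 × √[2(1 − ρ)], which is 0.29 at ρ = 0.5. The sample variance with n = 48 is then about 0.0841 + (2d²/3)(48/47). The half-width is t(47) × SD / √48, with t = 2.012.

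| d | SD | 95% half-width | Widening |
|---|---|---|---|
| 0 | 0.290 | 0.084 | – |
| 0.1 | 0.302 | 0.088 | 4% |
| 0.2 | 0.334 | 0.097 | 15% |
| 0.3 | 0.381 | 0.111 | 31.5% |

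At d = 0.2 the widening is 8% for ρ = 0 and 24% for ρ = 0.7.

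**Unequal losses.** The bias in A − B is d × (n A-first − n B-first) / N.

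- Half of one starting product's patients lost, nobody else: (10 − 20) / 50 = −0.2. The size is 0.2d, or 0.02 to 0.06 INR for d = 0.1 to 0.3.
- 12 lost, split 2/8/2 by starting product: (18 − 12) / 48 = 0.125. The bias is 0.125d, or 0.025 at d = 0.2.
- All 12 lost from one starting product: (20 − 8) / 48 = 0.25. The bias is 0.25d, or 0.05 at d = 0.2 and 0.075 at d = 0.3.
- 12 of 60 lost at random: the variance of the difference in losses between two starting products is 12 × (48/59) × [2 × (1/3)(2/3) + 2 × (1/3)(1/3)] = 6.51. Its SD is 2.55, and 2.55 / 48 = 0.053. One SD of the bias is therefore about 0.05d, or 0.01 INR at d = 0.2.

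**Simulation check** (ρ = 0.5, 1,500 runs per scenario, d up to 0.49). The paired t-test matched these formulas. Its 95% interval covered the true value in about 97% of balanced runs at d = 0.2, and in about 85% when all 12 losses fell on one starting product. A model with patient, phase and product terms had bias of at most 0.002, half-width 0.083 to 0.085 and coverage of about 94% to 97% in every scenario.

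**Against the 0.49 limit.** In the harshest case with d = 0.3 and no true product difference, the bias of 0.075 plus the half-width of 0.105 gives 0.18, well inside 0.49.

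**The case against.** The strongest reply is that none of this threatens the stated objective. The hypothesis in section 3 concerns a limit of 0.49, and even at d = 0.3 the balanced half-width of 0.111 is under a quarter of it. A wider interval is also conservative for an equivalence claim. This stands, and it sets the weight of the point.

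The size of d is also undocumented. Dose adjustment towards the 2.0 to 3.0 range works against sustained shifts. The TTR rule is two-sided, so it narrows spread more readily than it moves the mean. A d of 0.3 is about one full SD. This stands too, and the figures are conditional on it.

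Three stronger readings are tempting, and the protocol does not support them:

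- A reader might infer that the t-test throws away the protection of randomising to six sequences. It does not. Under balance the estimate stays unbiased, and only precision and robustness to imbalance are lost.
- A reader might infer that a phase term cures the missing run-in before phases 3 and 4. Section 4.4 says of the run-in that "The duration of three weeks for this phase is equivalent to about seven warfarin half-lives", and the later phases have no such period. What that leaves is carry-over of the previous product, which depends on the products differing. It is not a shift common to all patients, and phase terms do not remove it.
- A reader might infer that the model rescues patients whom the t-tests would drop. Pairwise t-tests also keep a patient for any completed pair.

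Nor can it be said that the method is simply left to a later analysis plan, because the protocol names the test.

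**Conclusion.** The point holds as a modest one about efficiency and robustness. The named analysis for mean INR and PT ignores the phase structure by which patients are randomised. For phase shifts of 0.1 to 0.3 INR the cost is a half-width 4% to 31.5% larger. With losses unequal by starting product there is a bias of 0.02 to 0.06 INR in the half-lost scenario, and of about 0.05d (one SD) if losses are random.

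These amounts alone are unlikely to overturn an equivalence conclusion at 0.49. They matter more for tests of difference at 5%, where power is lost under balance and the error rate can rise under strongly unequal loss.

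The result rests on three assumptions: all six product orders are used, the SD of paired differences is 0.29 (ρ = 0.5), and the phase shift takes the assumed values. The TTR exclusion makes unequal loss possible, but the protocol documents no rate.

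**What to change.** In section 4.6.2, replace the paired t-tests as the main analysis of mean INR and of mean PT with one crossover model per outcome. It should have fixed effects for product and phase (2, 3, 4) and a patient effect; a sequence term is optional. Report each of the three pairwise product differences with its confidence interval, and for INR read it against the 0.49 limit. Keep the paired t-tests as a sensitivity analysis.

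Add a sentence stating that this model does not remove carry-over of the previous product into phases 3 and 4, nor selection caused by exclusions after randomisation.

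The cost is a change of wording. No new data are needed. Phase uses two degrees of freedom, and a fixed sequence term, if included, uses five more between patients.

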## **1. Background**

### **1.1 Generic drugs**

In this introduction, we started describing that generic drugs represent a significant share of the drug market in Brazil and are completely incorporated in the country's health policies (1-4). We mentioned, however, that when it comes to the group of narrow therapeutic index drugs, which includes warfarin, even healthcare providers are suspicious of the equivalency of generic drugs to their branded counterparts (5-7,17-18). Next, we explained the technical requirement that generic drugs must fulfill in order to be considered equivalent to the brand medication, mentioning that some countries, but not Brazil, apply additional requirements to narrow therapeutic index drugs (7-12). Afterwards, we presented some studies that compared the effects of generic and branded warfarins. Randomized clinical trials did not show clinically meaningful differences between generic and branded warfarins, whereas observational studies brought more conflicting results. Nevertheless, none of these studies have used the generic and branded warfarins available in Brazil, limiting their applicability in our country (6, 13-16,19-21). Subsequently, we mentioned an issue that might arise when there is more than one generic drug available for a given brand medication: generics are devised to be equivalent to the brand medication, but not necessarily equivalent to each other (22). Finally, we presented the objectives of this project: run a randomized crossover clinical trial to assess whether the substitution of 1) branded warfarin by any of the generic formulations available in Brazil, or 2) substitution within the generic warfarins, is effective and safe for the patient with atrial fibrillation (AFib). We also added that patients with AFib diagnosis were selected because this was the most common diagnosis among the patients of anticoagulation clinics (23).

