## **2. Objectives**

### **2.1 Overall objective**

Determine, through the mean international normalized ratio (INR) of patients, whether there is therapeutic equivalence between brand and generic warfarin sodium tablets in patients with atrial fibrillation in Brazil.

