### 3. Hypothesis

The comparison of the mean INR between branded and generic warfarins is within the limit of 0.49 (two-sided, with a significance level of 5%) demonstrating therapeutic equivalence between them.

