##### **4.5.1 Primary outcome**

- Mean INR

The average INR of each patient will be compared when using the different warfarin formulations.

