#### **4.6 Statistical Method**

##### **4.6.1 Sample size**

At least 48 patients (8 in each group) will be needed in order to identify a clinically significant difference of 0.49 in the INR, considering a mean INR of 2.45 with standard deviation of 0.29, data reported for a branded warfarin in a published study (13). The sample was calculated based on the mean INR outcome, using the statistical method for quantitative outcomes (41) assuming  $\alpha = 5\%$  and  $\beta = 10\%$ , which result in a power of 90%. We plan to recruit 60 individuals (10 in each group) to compensate for possible dropouts or exclusions of patients.

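### The hypothesis is equivalence of mean INR within 0.49, but the analysis section names only ordinary paired t-tests and never ties them to that limit

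*Protocol*

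**What the plan says.** Section 2.1 of the Protocol asks "whether there is therapeutic equivalence between brand and generic warfarin sodium tablets", judged on mean INR. Section 3 attaches a limit: "The comparison of the mean INR between branded and generic warfarins is within the limit of 0.49", and adds the sidedness and level: "is within the limit of 0.49 (two-sided, with a significance level of 5%) demonstrating therapeutic equivalence between them". Section 4.5.1 defines the comparison within patients: "The average INR of each patient will be compared when using the different warfarin formulations".

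Section 4.6.1 uses the same 0.49 in another role. The sample is chosen "in order to identify a clinically significant difference of 0.49 in the INR", with SD 0.29, 5% significance and 90% power, giving 48 patients (8 in each of six sequences).

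Section 4.6.2 gives the analysis: "Paired-samples t-tests (also called dependent T-tests) will be used for the outcome of mean INR and PT". It sets 5% for all analyses. It mentions neither 0.49, nor a confidence interval, nor two one-sided tests, nor any other rule for concluding equivalence.

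Section 1.1 names a second question, whether "substitution within the generic warfarins, is effective and safe for the patient with atrial fibrillation". Section 3 states its limit for brand against generic only, and no section gives a limit for PT.

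**The concern.** An ordinary paired t-test asks whether the mean difference is zero. The hypothesis asks whether it is smaller than 0.49. These are different questions and can have different answers. Failing to reject zero does not show that the difference is small. Rejecting zero does not show that it is large enough to matter.

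The primary conclusion is at stake. Under the Protocol's own SD the sample is large relative to the limit, so the likely error is to report two products as different when the data place them well inside the Protocol's own definition of equivalence.

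This goes beyond a detail that a statistical analysis plan would normally fill in. The Protocol fixes an equivalence hypothesis with a limit and then fixes a test that does not address it. A plan that followed 4.6.2 would inherit the mismatch.

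**Working it through.** **Inputs from the Protocol.** Limit 0.49 (section 3). SD 0.29, 5% two-sided, 90% power and 48 patients (section 4.6.1). Paired t-test at 5% (section 4.6.2).

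**Assumed input.** The Protocol gives no SD for the within-patient difference. With SD 0.29 on each product and correlation ρ, it is SDd = 0.29 × √(2(1 − ρ)):
- ρ = 0: 0.29 × √2 = 0.41
- ρ = 0.5: 0.29 × √1 = 0.29

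**Step 1. Reproduce the 48.** The standard formula for detecting a difference between two means is n per group = 2 × [SD × (z₀.₉₇₅ + z₀.₉₀) / Δ]². With the Protocol's values, 2 × [0.29 × (1.960 + 1.282) / 0.49]² = 7.36, rounded up to 8. Then 8 × 6 sequences = 48. The figure therefore comes from a formula for finding a difference, which fits the plain reading of 4.6.2 as a test against zero.

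**Step 2. Precision with 48 patients.** The standard error is SDd/√48, and the half-width of the 95% interval is t₀.₉₇₅,₄₇ × SE with t = 2.012:
- SDd 0.41: SE 0.0592, half-width 0.119
- SDd 0.29: SE 0.0419, half-width 0.084

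A 95% interval inside ±0.49 therefore needs an observed difference no larger than about 0.37 (0.49 − 0.119) or 0.41 (0.49 − 0.084). The t-test is significant once the observed difference exceeds about 0.119 or 0.084. Any observed difference between those bounds is both significant and equivalent.

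**Step 3. How often the two rules disagree.** The chance of p<0.05 is from the noncentral t distribution with 47 degrees of freedom. The chance that the interval lies inside ±0.49 is for the 95% interval.

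| True difference | SDd | p<0.05 | 95% interval inside ±0.49 |
|---|---|---|---|
| 0.10 | 0.41 | 38% | over 99.9% |
| 0.15 | 0.41 | 70% | over 99.9% |
| 0.15 | 0.29 | 94% | over 99.9% |
| 0.20 | 0.41 | 91% | 99.8% |

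A 90% interval is narrower, so it passes at least as often.

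**Step 4. Sample size under an equivalence rule.** At zero true difference, 90% power with the 95% interval needs 12 patients in total at ρ = 0 and 7 at ρ = 0.5. With 48 patients the power exceeds 99.9%. At a true difference of exactly 0.49, the rule wrongly declares equivalence in 2.5% of trials with a 95% interval and 5% with a 90% interval.

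**Step 5. Period effects.** Take an assumed linear drift of g INR per phase. Across the six possible orders of three products, a given pair is one phase apart in four orders and two apart in two, so the drift adds g² × (4×1 + 2×4)/6 = 2g² to the variance of the paired difference.
- g = 0.1, SDd 0.41: √(0.1682 + 0.02) = 0.434, up 6%
- g = 0.2, SDd 0.29: √(0.0841 + 0.08) = 0.405, up 40%

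The signed phase gaps sum to zero over the six orders, so equal sequence sizes leave the mean difference unbiased.

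**The case against.** **The paired t-test can serve equivalence.** Two one-sided paired t-tests against −0.49 and +0.49, or the paired-t confidence interval, would use the limit directly. Section 3 already gives the limit, the sidedness and the level, and a statistical analysis plan not shown here could supply the interval rule. This stands in part. A reader might infer that the paired t-test is the wrong family of method, and the documents do not support that. What is missing is the link between section 3 and section 4.6.2. Read literally, 4.6.2 tests for zero difference, and the sample size was derived the same way.

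**False reassurance.** A reader might also infer that the written test could readily miss a difference at the limit and so pass non-equivalent products. The stated SD does not support that. With SD 0.29 on both products, SDd cannot exceed 2 × 0.29 = 0.58, even at correlation −1. With 48 patients, a true difference of 0.49 would then be non-significant in less than 0.01% of trials. With only 20 patients it would be 0.1% at SDd 0.41 and about 5% at SDd 0.58. Non-significance remains an invalid basis for claiming equivalence, but under the Protocol's figures the practical error lies in the other direction.

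**Period effects.** A reader might infer that ignoring period biases the comparison. The design is a "Randomized crossover controlled trial containing six treatment sequences" with equal planned group sizes, so a common drift costs precision only. At g = 0.2 and SDd 0.41 the SD becomes about 0.50, and the 95% interval at a true difference of 0.15 still lies inside the limit in over 99.6% of trials. A model with period terms is a preference, and its terms are normal content for a statistical analysis plan.

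**Conclusion.** The point holds in this form: the Protocol states an equivalence hypothesis with a limit, and its analysis section supplies no rule that can confirm or reject it. With 48 patients, SD 0.29 and an assumed correlation of 0 to 0.5, a true difference of 0.15 would be called significant in 70% to 94% of trials, although the interval satisfies the Protocol's limit in over 99.9%. The percentages rest on the assumed correlation and on the SD of 0.29, which the Protocol takes from a published study of one branded product. The logical gap depends on neither.

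The planned number of patients is adequate for an equivalence rule under the stated SD. The change is needed because it determines what the trial may conclude on its primary question.

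**What to change.** 1. In 4.6.2, state that for the brand against each generic separately, equivalence on mean INR is concluded only if the whole confidence interval for the within-patient mean difference lies between −0.49 and +0.49. The paired-t interval is sufficient.
2. Fix the interval level in advance and make it agree with section 3. A 95% interval matches the two-sided 5% stated there; a 90% interval corresponds to two one-sided 5% tests, and section 3 would then need rewording.
3. In 4.6.1, restate the rationale for equivalence within 0.49 and give the assumed SD of the within-patient difference. The number of patients need not rise under the stated SD.
4. For generic against generic, and for PT, either state a limit with its justification or report the interval descriptively without an equivalence claim. The Protocol contains neither limit, so choosing one is for the sponsor.
5. Optionally, estimate the differences from a model with formulation, period and sequence as fixed effects and patient as a random effect, for precision if INR drifts over the phases.

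Items 1 to 3 cost wording only. Item 4 needs the sponsor's clinical judgement if equivalence is to be claimed there. No extra patients or measurements are required.
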